This research project will develop mHealth BCC approaches to address key infant and young child feeding (IYCF) behaviours, caring practices, WASH practices, and health seeking behaviour in an emergency affected IDP population. A mHealth BCC component, if effective, could be a cost-efficient component to add to cash transfers that reach populations in insecure/inaccessible areas, as well as populations on the move. The interventions, if effective, have a high feasibility of being scaled up in Somalia and elsewhere around the world.

Using a randomised cluster-controlled 2x2 design, this study aims to assess whether a conditional cash transfer combined with mHealth BCC audio messaging, delivered through mobile phones, can improve vaccination coverage, child dietary diversity, breastfeeding practice and thereby reduce the risk of acute malnutrition in children aged 0-59 months, living in IDP camps near Mogadishu, Somalia.

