## Cash Transfer Intervention

Cash will be provided to households either as an unconditional or conditional cash transfer. All groups will receive cash transfers due to ethical reasons, as all households are considered to be suffering from extreme poverty and to be highly vulnerable. Randomization will be done at the cluster (camp) level. Households living in the selected camps will be listed and registered by the Concern cash distribution team.

The cash distribution will be done electronically each month and the specified amount will be sent to the registered SIM card of the beneficiary in US$. The cash transfers will be implemented by Hormuud Telecom via their EVC Plus money transfer service.[[2]](#footnote-3) Once the beneficiaries receive the cash transfer they can then use it to purchase items electronically or exchange for physical cash at a wide range of local shops. If they experience problems with use of the cash transfer they can contact the local Hormuud Telecom office for assistance. Problems can also be reported to the Concern beneficiary help line.

Cash transfers will follow the standard amounts set by the Somalia Cash Working Group based on a percentage of the Monthly Expenditure Basket (MEB). The cash transfers will be provided for 9 months. For the first 3-6 months the transfer amount provided will be that given during a humanitarian cash transfer programme; for the following 6 months the amount provided will be aligned with that given by social safety net (welfare) programmes.

The conditional cash transfer will require households with children, aged 0-59 months, to have first attended the local health clinic where they will receive a health screening, any necessary vaccinations, deworming, and vitamin A supplementation as required; and they will be issued with a child health record card. All the study camps have similar access to local health clinics. The health clinic visit will be verified by asking for the child health record cards during registration of the household for cash transfers.

Checks of child health card will be carried out monthly during the monthly monitoring household visits by CHWs. The check will monitor whether all children in the household 0-59 months are up to date on routine vaccination, vitamin A supplementation, and deworming.

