# Outcome measures

- Measles vaccination coverage - % of children 9-<59 months of age who received measles vaccine
- EPI vaccination coverage - % of children 0-<59 months of age who received all vaccines required by the national vaccination protocols
- Child diet diversity score of children 6-<24 months of age
- Parental/caretakers knowledge of BCC health and nutrition topics

The secondary outcomes of interest are:

- Incidence of acute malnutrition - MUAC<12.5 cm or oedema among children 6-59 months
- Incidence of mortality among children 6-59 months
- Exclusive breastfeeding prevalence - % of infants 0-5 months who were exclusively breastfed during the last 24 hours ​
- Incidence of child morbidity
- Causes of death ascertained by Verbal Autopsy

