# Quantitative Data collection

Quantitative data will be collected using questionnaires translated into the local Somali language, and addressed to the primary carer of the child included in the study. A household surveillance system will be set up to collect anthropometric data that will be used to evaluate whether the intervention changes the primary and secondary outcomes listed above. Data collection will be done monthly at the household level by a team of CHW, closely supervised by Concern Nutrition Supervisors and the Study Coordinator. The questionnaires will include the data collection listed below but note that not all variables will be collected each month. Figure 4 provides a schematic to explain the data collection plan for each month of the study.

Separate household, child (0-59 month), and Mother/questionnaires will be used.

(a) Household questionnaire: The data collected will include: camp name, HH ID, data of arrival, age, sex, region of origin, date of interview, reduced coping strategies index, household food insecurity access scale (HFIAS) score, food consumption score (FCS).

(b) Child (0-59 months) questionnaire: HH ID, personal ID, vaccination status, 7 day morbidity recall, 24 hour dietary recall, mid upper arm circumference (MUAC), and nutritional oedema.

(c) Mother/carer: HH ID, personal ID, age, parity, region of origin, clan, health and nutrition knowledge, diet diversity score

Those identified as malnourished or sick will be referred to local nutrition or health centres for treatment.

Figure 3 Schematic of data collection schedule

Full data collection will be undertaken at the time points marked in blue while a reduced questionnaire will be used at the other monthly data collection time points. This will enable effective monitoring of changes during the intervention period while reducing the burden on the participants and data collection team.

[figure not shown]

In the Somalia context, membership of clan and sub-clans is an important cultural and political factor. Clan membership is thought to influence vulnerability during crises and we will explore this hypothesis using the data we will collect on clan membership from all participants.

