# Data Analysis

Data analysis will be conducted using Stata v14 software. Difference-in-difference analysis will be used to describe differences between arms in hypothesised mediating variables such as health and nutrition knowledge. Linear and logistic regression models will be used to test the main hypotheses while adjusting for covariates that are found to be associated with outcome measures and may act as potential confounders on the causal pathway.

Primary analysis will be conducted based on intention to treat. Secondary analysis will use monitoring and adherence data to assess for any dose response effect associated with the BCC or cash interventions.

Qualitative data will be transcribed in Somali, translated into English, and analysed using the framework method for thematic analysis. Analysis will be conducted using Nvivo qualitative data analysis Software (QSR International Pty Ltd. 2012. Version 11).

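### The covariate rule for the main models contradicts itself and, as written, permits adjustment for mediators and selection by association with the outcome

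*Protocol*

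**What the plan says.** The Data Analysis section of the protocol assigns the main hypotheses to linear and logistic regression and gives this rule for adjustment: "adjusting for covariates that are found to be associated with outcome measures and may act as potential confounders on the causal pathway". It names no covariate and sets no limit on when a covariate must have been measured. The primary analysis is by intention to treat.

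The sentence just before the rule gives mediators a different treatment: "Difference-in-difference analysis will be used to describe differences between arms in hypothesised mediating variables such as health and nutrition knowledge". The paragraph after it reserves monitoring and adherence data for a secondary dose-response analysis.

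Three other places matter:

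- Outcome measures puts "Parental/caretakers knowledge of BCC health and nutrition topics" in the first outcome list, ahead of the outcomes labelled secondary.
- The Introduction sets out the assumed pathway: the combined intervention "can improve vaccination coverage, child dietary diversity, breastfeeding practice and thereby reduce the risk of acute malnutrition".
- Quantitative Data collection says "Data collection will be done monthly at the household level by a team of CHW", so many variables measured after allocation will be available as candidate covariates.

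**The concern.** The rule has two separate faults.

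**It mixes up two kinds of variable.** A confounder is a common cause of exposure and outcome. With camps randomised, a variable measured beforehand can differ between arms only by chance. A variable on the causal pathway is changed by the intervention. Conditioning on it takes out the part of the effect that runs through it. Intention to treat in a randomised trial targets the total effect of allocation, and a model that holds a mediator fixed estimates something else.

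**It selects on the outcome.** Covariates enter because they are found to be associated with the outcome. The estimate and its p-value then depend on which candidates survive the search, in a trial with only 20 randomised units.

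At stake is a diluted, possibly falsely null, result on either main hypothesis, or a positive result open to challenge as a product of covariate choice.

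**Working it through.** **1. Does the rule admit a mediator?** Take caregiver knowledge in the diet diversity model for hypothesis 2.

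- Association with the outcome: expected, since the messaging is meant to improve feeding through knowledge.
- Position on the pathway: yes. The protocol's own term covers "hypothesised mediating variables such as health and nutrition knowledge".
- Timing: the rule excludes nothing measured after allocation.

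Knowledge therefore passes if the association is observed, and an analyst who adjusted for it would be following the text.

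**2. The plan's own figures, as a yardstick.** The rule itself rests on no stated number. Inputs from Sample Size Calculations: 10 camps per arm, 65 children per camp, alpha 0.05 (taken as two-sided), power 0.8. Coverage: 64% baseline, ICC 0.06, hypothesised effect 20 points. Diet diversity: SD 2, ICC 0.01.

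Design effect = 1 + (65 − 1) × ICC. Effective n per arm = 650 / design effect.

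- Diet diversity: 1 + 64 × 0.01 = 1.64; 650 / 1.64 = 396.3; SE = 2 × √(2/396.3) = 0.142. With t on 18 df, the detectable difference is (2.101 + 0.862) × 0.142 = 0.421. The stated 0.42 reproduces.
- Coverage: 1 + 64 × 0.06 = 4.84; 650 / 4.84 = 134.3. With t on 18 df, the detectable increase from 64% is 16.0 to 16.1 points. Taking the variance at p = 0.5 gives 2.963 × √(0.5/134.3) = 18.1 points. The stated 18 is therefore on the cautious side, and nothing below depends on it.

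**3. What mediator adjustment does.** In a linear model let the total effect be Δ, of which a share q runs through variable M. The coefficient on allocation, with M in the model, is (1 − q)Δ. A simulation of 4,000 trials with the diet diversity inputs, a true effect of 0.42 and an assumed 0.5 SD shift in M gave:

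| Model | Estimated effect |
|---|---|
| Unadjusted | 0.42 |
| Adjusted for a baseline covariate | 0.42 (SE 0.139 v 0.142 unadjusted) |
| Adjusted for M, q = 50% | 0.21 |
| Adjusted for M, q = 100% | 0.00 |

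Baseline adjustment does no harm and gains a little precision. Only the on-pathway variable changes the estimate.

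**4. Power by share removed.** Power comes from the noncentral t on 18 df with noncentrality δ/SE, where δ = (1 − q)Δ. For coverage, SE = √{[0.64 × 0.36 + (0.64 + δ)(0.36 − δ)] / 134.3}. For example, at q = 50%, δ = 0.10, SE = √(0.4228/134.3) = 0.0561 and δ/SE = 1.78. For diet diversity, SE = 0.142 throughout.

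| q (assumed) | Coverage effect left | Power | Diet diversity effect left | Power |
|---|---|---|---|---|
| 0% | 20 points | 95% | 0.42 | 80% |
| 25% | 15 points | 74% | 0.315 | 56% |
| 50% | 10 points | 39% | 0.21 | 29% |
| 75% | 5 points | 13% | 0.105 | 11% |
| 100% | 0 | 5% | 0 | 5% |

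The documents give no q, so the whole range is shown.

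**The case against.** The strongest defence is that the phrase is loose wording for ordinary baseline confounders. The noun is confounders, hedged twice, and no mediator is named as a covariate for these models. The same section sends mediators to a difference-in-difference description and adherence data to a secondary analysis, so the authors evidently distinguish the two. On that reading no effect is removed. With 20 camps, chance imbalance is a real concern and adjustment for prognostic variables is legitimate. A covariate list may properly be left to the SAP.

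Much of this stands. A reader might infer that the plan will adjust for mediators and so will lose its effect; the text only permits this. A reader might also infer that nearly all of the conditionality effect would vanish, because the condition requires households "to have first attended the local health clinic where they will receive a health screening, any necessary vaccinations". The documents do not support that step. They give no mediated share, and clinic attendance is not among the listed questionnaire variables. Nor are health cards requested at registration in the unconditional arms, so that check gives no covariate comparable across arms. Knowledge is the only variable the protocol itself names as a mediator.

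Two things do not yield. Describing arm differences in mediators does not bar them from the main models, and neither does using adherence data in a secondary analysis. Selection by observed association with the outcome also remains on the benign reading. The absence of a covariate list is not the point. The protocol states a selection rule, and a SAP limited to pre-specified baseline covariates would have to depart from it.

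**Conclusion.** Wrong as written. The rule contradicts itself, fits poorly with an intention-to-treat estimate, and permits both mediator adjustment and outcome-driven covariate selection in the models for the main hypotheses. It does not show that the effect will be lost.

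If an on-pathway variable is adjusted for, the loss runs from nothing to the whole effect according to q. At q = 50%, power falls from 95% to 39% for coverage and from 80% to 29% for diet diversity. These figures take the plan's cluster size and ICCs as given and keep the unadjusted form of the standard error. They assume no unmeasured common cause of mediator and outcome, and use a linear approximation. The protocol also specifies logistic models, for which (1 − q) is only approximate. The effect of outcome-driven selection was not quantified.

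**What to change.** In Data Analysis, delete both the clause that selects covariates by their association with the outcome and the reference to the causal pathway. Replace them with wording such as:

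*Primary models adjust only for variables that are specified in advance and measured before the intervention (such as the baseline value of the outcome, child age and sex) and for the other randomised factor. No variable measured after allocation enters a primary model. Mediators are examined only in separate, labelled analyses.*

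In the conditional arms the clinic visit comes before registration for cash, so the baseline value should be one recorded before that visit.

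The cost is a few sentences. No new data are needed, since a difference-in-difference analysis already presupposes measurements before the intervention. The existing mediator and dose-response analyses can stay as they are.

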# Staff Training and Study Management

UCL will conduct face to face training of the study staff. The training locations used previously have been in either Mogadishu, Nairobi or Hargeisa, depending on the people involved and the security conditions pertaining at the time. Standard team training methods will be used including sessions on background theory, practical training on anthropometric measurements, role playing interview procedures, and piloting. Standardization tests will be performed to assess the participant’s ability to take accurate and precise measurements, and to record and enter data reliably. Participants who fail to achieve minimum standards will receive further training and/or not be deployed.

Community Health Workers (CHWs) will be selected from within the study communities and will receive training on anthropometric measurement, identification and referral of malnourished children and other people requiring medical attention, and referring young children for vaccinations. CHWs will also be trained on identification and referral of children with suspected malaria, diarrhoea, and pneumonia. CHWs will be recruited after administering a test and a face to face interview with Concern Health and Nutrition staff members in partnership with local authorities.

The Study Coordinator will provide regular on the ground support during data collection and, when this is not possible, will provide regular communication and support via internet and phone communication. The Study Coordinator and the Field Coordinator will supervise all field-teams. All the study team except the Study Coordinator will be local staff and will be based in the Mogadishu area, minimizing the risk of staff shortages due to road or airport closures.

# Risk Management

Currently, Mogadishu is considered relatively secure, although there are intermittent attacks by armed opposition groups against government officials and military forces allied with the government. There are also incidents of kidnapping for ransom and other criminal activities.

It is anticipated that Concern will have continued access to research areas in Mogadishu, with no serious escalation in conflict or deterioration in the political situation which would cause research areas to become inaccessible to either Concern or its partner staff. A critical assumption is that there will be no deterioration in the security situation which would make the presence of national or international staff untenable within the study area. We presume continued effective and consistent support from all stakeholders involved in this project.

Table 3 Risks and Contingencies/Alternative Strategies

| **Risk Factors** | **Contingencies/Alternative Strategies** |
| --- | --- |
| Inaccessibility of project  sites due to security concerns | A researcher of Somali origin from Kenya will oversee the research, closely supervising Somali national staff with strong capacity to undertake the research. Flexibility in approach is of paramount importance. Detailed options for re-scheduling, relocating, or modifying study activities in response to changes in the security conditions or other factors will be developed at the start of the project. Regularly review of security status with local authorities and institutions will be done and all teams on the ground will be kept well informed with security updates. |
| Lack of support/political goodwill by the community | All efforts will be made been made to align the research activities to the usual community household activity calendar/schedule whilst ensuring they will not be time-consuming. |
| Natural disaster (diseases, drought, pests, floods, etc. of unprecedented magnitude) | Deliberate efforts will be made to ensure that the project is complemented by other ongoing emergency interventions. In case of a large scale disaster, emergency funds from other donors will be mobilized. |
| Political stability at national level does not  provide enabling environment | A flexible implementation strategy has been designed. All relevant government officials at national and regional level will be kept well informed about the project through an inception meeting. In addition the community will be kept well informed of program. |
| Unnoticed and forceful eviction of research participants from IDP camps | Proper follow up and defaulter tracing mechanism will be employed to ensure that as many as possible participants complete the entire study duration. |
| Discontinuation of cash transfers which causes participants to seek humanitarian assistance in other areas. | Concern will work with donors, MOH and partners to conduct the study in areas most in need of CTP over the program period. |

During the previous REFANI-S study, Concern and UCL have developed robust approaches to ensure the quality of quantitative and qualitative data collection in a difficult security context where international researchers are generally not allowed full access and where many local staff have not had the opportunity to pursue advanced training. The HR strategy has been to recruit strong Somali nationals and invest heavily in their training and support, including UCL by researchers that provide regular training, mentoring and close supervision.

The Study Coordinator is from Kenya and is able to visit the study sites regularly and provide technical support to the teams.

In addition, the team on the ground are supported by the Concern Somalia Health and Nutrition Coordinator, Dublin based health, nutrition and research advisors, as well as the Somalia Programme Director, who has experience in research and program management. This approach has allowed Concern and UCL to build up a strong cadre of Somali research staff for quantitative and qualitative data collection. This team will be utilized during the CINS research and the same approach used, thereby building local capacity and ensuring a deep understanding of the local context.

# Ethical Review

Ethical approval has been obtained from the Ministry of Health, Mogadishu (Ref Number: MOH&HS/DGO/0993/Jun/2018) and is being sought from the Research Ethics Committee of University College London. The study will be registered with ISRCTN. Informed verbal consent will be obtained from camp leaders in all camps before the start of data collection. Informed consent, verbal and written, will be sought from caregivers at the household level following a detailed explanation of the study objectives and the data that will be collected. In addition, they will be informed about their right to withdraw from the study and that participation or withdrawal from the study will not affect their entitlement to humanitarian assistance. All data collection procedures will ensure the anonymity of the respondents. This includes the removal of any spatial data from datasets that could be used to identify the precise location of respondents.

# Coordination with Stakeholders and Results Dissemination

Sub-national and national cluster meetings as well as inter-cluster coordination meetings led by the MoH, UNICEF, and OCHA already exist as forums for information sharing. Sub-national Nutrition Cluster coordination meetings are very useful for information exchange which feeds into the National Nutrition Cluster assessment and response to the situation.

Concern is a member of the Nutrition Cluster’s Assessment and Information Management working group (AIM WG) which is mandated to vet and validate all studies done by nutrition partners and will therefore present the study protocol to the group for their validation before start of the study implementation. Concern will also keep the group informed about the study progress by periodically presenting the progress in the AIM WG’s monthly meetings.

Concern is also a member of both the Food Security Cluster and Cash WG which provide coordination and sector strategies. In these platforms, agencies share information regarding their areas of work and what activities they are doing in specific area. Concern will therefore keep both cluster and WG members informed about the research study area and interventions so that duplication of activities will be avoided.

